## Abstract

**Background:**

Climacteric stage women experience significant biological, psychological and social changes. With demographic changes being observed in the growing number of climacteric stage women in Mexico, it is important to improve their knowledge about the climacteric stage and its potential associated problems, encourage their participation in screening programs, and promote the acquisition of healthy lifestyles.

At Mexican health care institutions the predominant health care model for climacteric stage women has a biomedical perspective. Medical doctors provide mostly curative services and have limited support from other health professionals. This study aims to design an integrative health care model (IHCM: bio-psycho-social, multidisciplinary and women-centered) applicable in primary care services aimed at climacteric stage women.

**Methods/Design:**

We present the design, inclusion criteria and detailed description of an IHCM. The IHCM consists of collaborative and coordinated provision of services by a health team, which is involves a family doctor, nurse, psychologist, and the woman herself. The health team promotes the empowerment of women through individual and group counseling on the climacteric stage and health related self-care. The intervention lasts three months followed by a three-month follow-up period to evaluate the effectiveness of the model. The effectiveness of the model will be evaluated through the following aspects: health-related quality of life (HR-QoL), empowerment, self-efficacy and knowledge regarding the climacteric stage and health-related self-care activities, use of screening services, and improvement in lifestyles (regular leisure time physical activity and healthy diet).

**Discussion:**

Participation in preventive activities should be encouraged among women in Mexico. Designing and evaluating the effectiveness of an integrative health care model for women at the climacteric stage, based on the empowerment approach and focus on health-related self-care to improve their HR-QoL is pertinent for current health conditions of this age group.

**Trial registration:**

The study is registered at the ClinicalTrials.gov (NCT01272115).

## Background

The climacteric stage is the transition from the reproductive to the non-reproductive period during a woman's life [1], and comprises 2 to 8 years before and after menopause [2], and coincides with a complex period in life due to biological, psychological and social changes.

Two circumstances motivated the design of this study. One is related to the unfelt and unsatisfied health needs of climacteric stage women; the other is related to the existing supply of health services in Mexico to the care of women at this stage.

### Health needs and existing supply of health services in Mexico for climacteric stage women

A need arises when one sees a difference between the situation considered as optimal and the actual observed situation; the difference to be reduced is then the need. In the health field, the felt need relates to the perception people have about their health problems or whatever they want to receive from the health services. Unlike a need that is not felt, there exists a need that people do not perceive, but it must be satisfied to maintain, restore or improve their health [3].

Increase in life expectancy has also caused an increase in the proportion of climacteric stage women with respect to the general population. Traditionally, climacteric stage women seek medical attention when they perceive health problems attributed to this stage such as severe climacteric symptoms, osteoporosis-related fractures, symptoms and/or complications of chronic diseases. Regarding the unfelt and unsatisfied need, most women do not perceive the need to prevent or detect such health problems early. These situations result in delayed health seeking-behavior for these problems, which in turn represent a significant burden for health care systems and for the society due to the high costs of health care, decreased quality of life and premature death [4-6].

In Mexico, a high proportion of women in the climacteric stage experience important biological, psychological and social changes; 50-70% report climacteric symptoms [7,8], 45.6% depression and other mood and sleep disorders [9], 31.1% suffer from hypertension, 16.7% suffer from diabetes [10,11]; the prevalence of hip fractures secondary to osteoporosis is 169 per 10,000 women-years [12], of breast cancer is 27.4 per 100,000 woman-years, and of cervical cancer is 19.2 per 100,000 woman-years [13]. This situation is worsened by women's overall limited knowledge about the potential health problems associated with the climacteric stage, and about the necessary preventive measures, indicated by their low participation in screening programs for chronic diseases and their unhealthy lifestyles (high proportion of physical inactivity and low consumption of fruits, vegetables and foods rich in calcium [8,11,14]), which impede a better overall health and quality of life.

Regarding the existing supply of health care for climacteric stage women (how the need is being met), Mexico has a fragmented health system, composed by Social Security institutions, the Ministry of Health (MoH) and private providers. The Mexican Institute of Social Security (IMSS) is a nation-wide social security institution that provides health and social services as well as economic benefits to formal sector workers and their families (approximately 48 million). While the MoH is central authority in charge of the policies and design of programs and while the provision of care is decentralized through the MoH in the 32 states, while granting each a certain autonomy, MoH provides health care to people without social security, mostly through the System for Social Protection of Health [15].

Despite the existence of preventive programs, most health care for climacteric women is based on a biomedical model in which a curative perspective predominates without support or with very limited support from other health professionals, where the relationship between health providers and patients is usually justified by authoritative professional knowledge. This model gives more importance to medical care for biological symptoms and minimizes the relevance of the psychogical and social changes that happen during the climacteric period.

### Interventions targeted at climacteric stage women

Most interventions for climacteric stage women have focused on informing/educating women about preventing certain diseases. Some studies have developed educational strategies to prevent osteoporosis [16] or to improve healthy diet [17], and have also aimed to improve physical activity in menopausal women, demonstrating the feasibility and effectiveness of moderate and rigorous physical activity, which in turn improves muscle strength, blood pressure, bone density and health-related quality of life (HR-QoL) [18-20]. Other studies have examined the impact of information about healthy behaviors, stress management and possible treatments during the climacteric stage; these studies have reported the favorable effect of education groups on the participants' knowledge, which is manifested by perceived ease in dealing with the changes of this stage, increase of healthy habits and increased sexual interest, when compared with a control group [21,22]. In climacteric women, as in the general population, interventions that incorporate cognitive-behavioral strategies, such as individual and group counseling to facilitate changes in lifestyle, have greater positive effect on vasomotor symptoms, psychological distress, self-efficacy, satisfaction with care and cardiovascular risk factors when compared to printed or verbal information [23-28].

### Integrative health care model and the empowerment approach

In the 1980 s, the biomedical model was strongly criticized in the middle of severe economic crises in many countries including Mexico. Alternative models that integrated biological, psychological and social areas gained momentum [29]. In 1994, M. Flint [30], highlighted the relationship among the biological, social and psychological factors that women face during menopause, highlighting the need for women to receive bio-psycho-social care at this stage.

The integrative health care model (IHCM) [31] includes a multidisciplinary approach based on a non-hierarchical combination of conventional medicine with complementary and alternative medicine, which promotes the harmonious continuity in decision-making and care that should be focused on the patient. The IHCM is based on a specific set of core values that include the goal of addressing health care in a holistic manner, and promoting personal health and wellbeing. The multidisciplinary approach of the IHCM is based on the collaborative participation of health team members, their mutual respect and a shared vision between them and the patients. This circumstance allows each provider and each patient to contribute their knowledge and particular skills to focus on providing health care to persons within individual care plans. In the experimental field in both developed and developing countries, attempts to implement the IHCM have been made. The study results showed that the IHCM allowed increased use of preventive services, improved health education and health outcomes [32,33]. The integrative care model is consistent with the empowerment approach. Empowerment is the social process of recognizing, promoting and enhancing the capacity of people to meet their needs, solve their problems, and mobilize the resources needed to take control of their lives [34]. The goal of patient empowerment is to build the patients' capacity for self-care, facilitate the process of obtaining experiences to identify problems (health needs), set goals related to their own health care, identify personal and social obstacles, develop solutions, consider the possible consequences of alternative solutions and make appropriate decisions for themselves [35-37]. The empowerment approach is linked to the theory of self-determination which supports the empowering of patients to be more independent in their self-care, and raising the possibility of long-lasting changes in health-related behaviors [38]. The counseling focused on the problems perceived and prioritized by the individual considers empowerment as an approach that also includes cultural aspects.

Interventions aimed to potentiate individual (or social) resources to prevent health damage or solve health problems implicitly adopt an empowerment approach to enable people to improve their quality of life by increasing the power to control their problems. For example, it has been shown that individual and group counseling on health-related self-care of patients with chronic diseases based on the empowerment principles, taking their cultural characteristics into account, achieved positive effects on HR-QoL, knowledge about the disease and related self-care, satisfaction with care and metabolic control compared with the control group (telephone counseling on metabolic control and traditional education) [39,40]. In addition, patients empowered in health-related self-care used fewer medical appointments, resulting in significant savings for health services [41].

### Conceptual model and objectives of the study

This framework sets the groundwork to address the health needs of climacteric stage women through an intervention that comprises, in an integral manner, their bio-psycho-social needs (Figure 1) and allows women to have greater control over the climacteric stage through acquiring knowledge, building on and utilizing individual strengths, making informed choices, setting personal goals, skills and attitudes necessary for better management of their environment and health-related self-care, which is called empowerment.

**Figure 1 F1:**
[figure not shown]
**Conceptual model of integrative health care for climacteric stage women**.

The characteristics of population, structure and processes of care within social security allows the implementation and testing of an integrative health care model (IHCM) for climacteric stage women (Table 1). The lessons learned from this first intervention that will be implemented in social security settings will provide further elements and evidence to eventually propose a study aimed at the population with social security in other developing countries. This work aims to develop an IHCM applicable in primary care services (family medicine clinics) for climacteric stage women. The effectiveness of the model will be evaluated through the following aspects: a) improved HR-QoL; b-d) increased empowerment, self-efficacy and knowledge regarding climacteric stage, and health-related self-care activities; e) increased use of screening services for breast cancer, cervical cancer, diabetes and hypertension; f-g) improved lifestyles: regular leisure time physical activity and healthy diet.

**Table 1 T1:** Structure and population characteristics of health institutions in Mexico

	Mexican Institute of Social Security	Ministry of Health
Population	Formal sector workers and their families	People without formal employment contracts, or unemployed and the rural population
Organization	Centralize	Decentralize
Drug acquisition, laboratory and screening tests	Covered by the social insurance	Covered partially by the insurance + out of pocket payments
Medical doctors	1.4 per 1000 habitants	1.3 per 1000 habitants
Nurses	2.0 per 1000 habitants	1.7 per 1000 habitants

## Methods/Design

A field trial with one intervention and one comparison group, with ex ante and ex post measurements will be conducted in two IMSS primary care clinics in Mexico City. The clinics will be selected for convenience; each clinic must have more than 20 family doctors' offices and available space for the intervention (consulting room and an area for group counseling) and should have accepted to participate in the study; The intervention will be conducted in one clinic and the other clinic will serve as a comparison group, where the usual care for climacteric stage women will be observed.

The study population will consist of women affiliated with IMSS, between 45 and 59 years of age with a maximum of 5 years after menopause. The women should be users of the clinic, and should not have mental conditions that would prevent them from understanding the information or from taking independent decisions (dementia, mental retardation or psychosis), a physical disability that would impede them from participating (hearing loss, diseases affecting physical mobility as severe forms of rheumatoid arthritis), medical diagnosis of depression, diabetes mellitus, hypertension, renal or liver failure, and/or cancer, because patients with these diseases require specific care provided by several specialists. All women must agree to participate in the study through written informed consent.

The project was authorized by the National Research and Ethics Committee of the IMSS.

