### Sample size

The sample size for the primary outcome (HR-QoL) was estimated by using the formula to test change in the mean of two normally distributed samples in longitudinal studies [50]. An average increase of at least 10 points in one or more domains of WHQ23 in the intervention group compared with control group women was considered to be clinically relevant. The assumptions included: a mean HR-QoL score of 64.9 points (standard deviation of 23.4 points) in the domain of general well-being [51], α = 0.05 (for one-sided hypothesis) and β = 0.20. The number of women by group, assuming a drop-out rate of 20% will be 107.

We also estimated a sample size for regular leisure time physical activity considering that this is the outcome variable more difficult to achieve. It was assumed that only 17% of women in Mexico engaged in some type of regular leisure time physical activity [11] and a positive increase of at least 10% will be achieved after women participation in the IHCM. For this calculation, we used the formula to test the difference of proportions between two populations [50] with a = 0.05 (one side) and the power of 80%. The total number of women by group to include assuming a drop-out rate of 20% will be 207.

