### Statistical analysis

The women characteristics of each intervention and comparison groups will be compared by using the Chi-square test to ascertain whether the groups were equivalent.

The effects of intervention for categorical outcome variables (regular leisure time physical activity, healthy diet) will be measured by comparing the baseline and post-intervention evaluation stages for differences in these variables using Chi-square test. Absolute percentage differences and corresponding 95% confidence intervals will be calculated.

Scores for the HR-QoL on the WHQ23 scale, the self-efficacy on the PHS-ES scale, the empowerment on the short form scale, knowledge about the climacteric stage, and menopause and self-care-related activities will be calculated according to the scoring algorithms. Measures of central tendency and distribution will be examined for these variables at the different measurement periods. The differences in the baseline and post-intervention stages for outcome variables will be compared within each group, and differences between the groups will be compared using the differences-in-differences (D-in-D) estimator [52]. The generalized linear model (GLM) will be used to assess changes in the main outcome variable controlling for baseline measures and other study variables as covariates. The GLM methods allow for modeling the correlation of the repeated observations on the same subjects [53].

The p value <0.05 will be considered as statistically significant. The analysis will be performed with the Stata 11.0 statistical software (Stata 11.0, Stata Corp; College Station, TX).

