## Discussion

In primary care services, it is essential to provide a source of care that has continuity and coordination, and comprehensively covers the health needs of people. The constraints resulting from limited resources and restrictive organizational characteristics of institutionalized healthcare allows a limited range of changes, and these circumstances promote that innovative healthcare models should be carefully designed and evaluated to demonstrate healthcare service relevance and feasibility. Relevance, in this case, refers to meeting the health needs of climacteric stage women and to demonstrating its potential benefit. Feasibility means that the new model of care is applicable in the local context. An integrative health care model (bio-psycho-social, multidisciplinary and women-centered) with the empowerment approach may be a better alternative to ensure that women engage in their self-care and understand its importance to their present and future health and quality of life. The evaluation of the effectiveness of this research-based model can guide the feasibility of extending it into an operational model through a specific program.

The possible limitations of the study may include the following:

It was decided to perform the intervention in one clinic, taking another as a control to prevent women from both groups from communicating and transmitting information between them. However, the implementation of the study in two clinics may result in difference baseline characteristics of women in both groups. To overcome this limitation in the data analysis step, the regression methods will be used to adjust the results of the study for possible differences between groups.

Furthermore, the baseline evaluation can affect women in the control group resulting in them seeking counseling regarding the climacteric stage, attending screening programs, and changing their lifestyles.

The request for voluntary collaboration of family doctors and women could result in better doctors and women with healthier lifestyles agreeing to participate. Previous studies have reported that patients with unhealthy lifestyles are usually reluctant to participate. To confirm or disregard this limitation we will apply a short list of questions about the general characteristics and lifestyles to women who do not agree to participate in the study.

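### With one clinic per arm, a clinic-specific change over the six months cannot be separated from the intervention effect; this limitation is not named, and the stated alpha and power hold only if clinics do not vary in change

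*Protocol article*

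**What the plan says.** **Design.** The Methods/Design section states that "The clinics will be selected for convenience" and that "The intervention will be conducted in one clinic and the other clinic will serve as a comparison group". It describes a field trial with a comparison group and does not claim randomisation. Outcomes are measured at baseline, three months and six months.

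**Sample size.** For the primary outcome (WHQ23) the target is "An average increase of at least 10 points in one or more domains of WHQ23", assuming "a mean HR-QoL score of 64.9 points (standard deviation of 23.4 points) in the domain of general well-being" and "α = 0.05 (for one-sided hypothesis) and β = 0.20". The result is: "The number of women by group, assuming a drop-out rate of 20% will be 107". A second calculation, for physical activity, gives 207 per group. Neither contains a clinic term.

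**Statistical analysis.** Groups are compared by difference-in-differences (D-in-D), with a generalised linear model controlling for baseline and covariates. The only correlation mentioned is between repeated measurements on the same woman. Significance is p<0.05. Baseline characteristics are compared "by using the Chi-square test to ascertain whether the groups were equivalent".

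**Discussion.** Separate clinics are used to stop women in the two groups from exchanging information. The article concedes that women in the two clinics may differ at baseline and continues: "To overcome this limitation in the data analysis step, the regression methods will be used to adjust the results of the study".

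**The concern.** When each arm is a single clinic, the arm indicator and the clinic indicator are identical columns in any model. Whatever happens in one clinic and not in the other between baseline and six months (a change of staff, a local screening drive) enters the estimated effect in full. No covariate on the women can separate it.

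Such changes are plausible on the article's own account. Use of screening is an outcome, and in the control clinic screening is delivered by clinic nurses on demand. Family doctors are invited and trained in the intervention clinic, and the Discussion accepts that those who volunteer may be the better doctors.

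The Discussion wants the results to guide extension of the model into routine operation. That needs inference about the model of care. The planned p-value answers a narrower question: whether these two clinics changed differently by more than sampling of women would explain.

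**Working it through.** **Inputs from the Sample size section.** Difference 10 points; SD 23.4; one-sided alpha 0.05; power 80%; 107 per group with 20% drop-out, so 107 × 0.8 = 85.6, about 86 analysed. For physical activity, 207 × 0.8 = 165.6, about 166 analysed.

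**Assumed.** The ICC of change between clinics (not in the documents), and 23.4, which is the SD of a score, used as the SD of change. With equal variances the SD of change is 23.4 × √(2(1−ρ)), which equals 23.4 when the within-woman correlation ρ is 0.5.

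**1. The plan's own figure.** n = 2 × [23.4 × (z_α + 0.842)/10]².
- One-sided, z_α = 1.645: n = 67.7, so 68, and 68/0.8 = 85. This is not 107.
- Two-sided, z_α = 1.960: n = 85.95, and 85.95/0.8 = 107.4. This matches.
- One-sided on change scores also gives about 107 to 108 if ρ is about 0.37, but no ρ is stated.

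So 107 can be recovered, but its sidedness is unclear. Every version treats women as independent and sets clinic variance to zero.

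**2. Degrees of freedom.** Two clinics minus two arms leaves 0 between-clinic degrees of freedom. This needs no assumption. Clinic variance cannot be estimated from the trial's own data.

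**3. Effect on alpha and power.** With m women analysed per clinic:
- Design effect: DEFF = 1 + (m − 1) × ICC
- Actual one-sided alpha = 1 − Φ(1.645/√DEFF)
- SE = 23.4 × √(2 × DEFF/m)
- Best-case power = Φ(10/SE − 1.645)

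Power is best case because it treats the ICC as known. For m = 85.6 and ICC = 0.01: DEFF = 1 + 84.6 × 0.01 = 1.846. Alpha = 1 − Φ(1.645/1.359) = 0.113. SE rises from 3.58 to 4.86. Power = Φ(10/4.86 − 1.645) = 0.66.

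| Assumed ICC | Alpha, 86 per clinic | Power, 86 per clinic | Alpha, 166 per clinic | Power, 166 per clinic |
|---|---|---|---|---|
| 0 | 0.050 | 0.875 | 0.050 | 0.988 |
| 0.001 | 0.057 | 0.85 | 0.064 | 0.98 |
| 0.005 | 0.084 | 0.76 | 0.112 | 0.89 |
| 0.01 | 0.113 | 0.66 | 0.156 | 0.77 |
| 0.05 | 0.236 | 0.34 | 0.294 | 0.36 |

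All powers are for the 10-point WHQ23 difference.

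**4. Which figures depend on the SD.** The SD cancels out of alpha, so the alpha columns rest on the ICC alone. Power does depend on it. At ICC 0.01 and 86 per clinic:
- ρ = 0.37: SD 26.27, SE 5.46, power Φ(10/5.46 − 1.645) = 0.57
- ρ = 0.7: SD 18.13, SE 3.76, power Φ(10/3.76 − 1.645) = 0.84

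**5. More women do not cure it.** As m grows, SE tends to 23.4 × √(2 × ICC), which is 3.3 points at ICC 0.01 and 7.4 at 0.05. For 80% power SE must be at most 10/(1.645 + 0.842) = 4.02. That requires ICC ≤ (4.02/23.4)²/2, about 0.015. Above that, no number of women from these two clinics gives 80% power.

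**The case against.** **Disclosure.** The design is stated openly: convenience clinics, a comparison group, no claim of randomisation, a sound reason for separate clinics (contamination), and limits on generalising beyond the institution. This stands. It makes the remedy mainly one of wording, but it does not make the stated alpha and power unconditional.

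**A stronger reading of the Discussion.** A reader might infer that the authors claim regression will separate clinic from intervention. The text does not say so. The limitation to be overcome is the one in the preceding sentence, differing baseline characteristics of the women, and regression is an ordinary remedy for that. The supportable criticism is that overcome is too strong a word even there, since only measured characteristics are adjusted, and that clinic-specific change is not mentioned.

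**Constant clinic differences.** A reader might also infer that any difference between the clinics biases the result. D-in-D removes differences that are constant over time, measured or not. Only differential change remains, so the ICC that matters is that of change.

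**Size.** The documents give no ICC. At 0.001 the alpha is 0.057 and power 0.85, close to nominal. It would go too far to state any single figure as the trial's true type I error. Two-sided calculations give larger alphas (about 0.15 at ICC 0.01 with 86 per clinic), but the Sample size section specifies one-sided, so the one-sided figures are used here.

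**Chi-square tests.** The planned adjustment is not made conditional on them. The point that a non-significant test does not show equivalence is correct but minor.

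**Conclusion.** The concern holds in a bounded form. Without any assumption: arm and clinic coincide, between-clinic degrees of freedom are 0, the planned analyses cannot remove a clinic-specific change over six months, and the Discussion does not say so. The stated 5% one-sided alpha and 80% power are conditional on zero between-clinic variance in change, and the article does not state that condition.

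The size depends on an assumed ICC of change. Over 0.001 to 0.05 with 86 women per clinic, actual one-sided alpha runs from about 0.057 (hardly affected) to 0.236. The fall in best-case power from 0.875 to 0.66 at ICC 0.01 further assumes an SD of change of 23.4. The documents do not support saying that the trial is uninformative or that its error rate is known to be a particular value. They support saying that a significant result would show that these two clinics changed differently, and that attributing the difference to the care model rests on an assumption the trial cannot test.

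**What to change.** 1. **Discussion, limitations.** Replace the opening words of the regression sentence with text to this effect: regression and D-in-D reduce bias from measured differences between the women and from clinic differences that are constant over time, but the estimate still combines the intervention effect with any change specific to one clinic during the study.
2. **Sample size.** State that alpha and power are conditional on zero between-clinic variance in change, and make the sidedness explicit, since 107 matches a two-sided calculation while the text says one-sided.
3. **Statistical analysis.** Pre-specify a sensitivity table for the primary D-in-D effect using SE² = SE_ind² + 2σ²_clinic, where σ²_clinic is the ICC times the variance of change, over a range such as 0.001, 0.005, 0.01, 0.02 and 0.05. Report the ICC at which the conclusion is lost. For example, with an observed effect of 10 points, SE 3.58 under independence and one-sided 5%, significance is lost when DEFF exceeds (10/1.645)²/3.58² = 2.89, so at an ICC of about (2.89 − 1)/84.6 = 0.022.
4. **Allocation.** Draw by lot which of the two consenting clinics receives the intervention; both must have the space for it. This prevents selective assignment. It does not separate clinic from intervention or restore degrees of freedom; that would need several clinics per arm.
5. **Minor.** Describe baseline balance with standardised differences rather than a test of equivalence.

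The cost is a few sentences, one table and a lot, together with a weaker claim.
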